### Recruitment {15}

According to the sample size calculation, this trial requires 320 patients in total. This project uses online media promotion, bulletin board in the hospital, recruits from outpatient visits, and other ways to recruit subjects with stiff shoulders in the Orthopedic Department Outpatients of Shuguang Hospital, Shanghai First People's Hospital, and Shanghai Baoshan District Hospital of Integrated Traditional Chinese and Western Medicine. The participants will undergo two initial diagnostic screenings conducted by clinicians at each research center. The clinicians responsible for diagnosis and screening are unaware of the random grouping. At the scheduled clinical visit, the study clinicians will briefly explain the study to the participants. If interested, the clinicians will assess whether the participant meets the eligibility criteria. If the participant is eligible and agrees to participate, the clinicians will obtain informed consent and enroll the participant. Before signing the informed consent, participants can discuss the study details with the clinicians and ask questions. After enrollment, full-time research assistants will conduct physical and imaging examinations and assign the treatment based on randomization.

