### Allocation {16a} {16b}{16c}

Eligible subjects who meet the test and research criteria will be randomly assigned into two groups, the trial group and the control group, in a 1:1 ratio. The random number table used for the randomization process is generated by statisticians at Shanghai University of T.C.M. and is not accessible to anyone else involved in the study. The randomization will be stratified by participating site and done in blocks of four. Each subject can only register and be randomized once, and their information cannot be deleted from the database. The clinicians will identify patients with frozen shoulder and confirm their eligibility using a CRF completed by a designated individual in the shoulder team. The recruiting clinician will then contact the statistical staff for randomization. The hospital staff will be informed of the allocation, but not the patient. The patient will be fully informed about the allocated therapy and given an information sheet to review before deciding to consent, which can take up to a week. If the patient does not consent, their reason for not doing so will be briefly recorded in a CRF. Those who consent will complete baseline forms and receive further treatments.

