## Statistical methods

### Outcomes {20a}

The data will undergo encoded analysis and various patient details, such as their baseline information, range of motion, CMS, VAS, MPQ, PPI, duration of symptoms before treatment, and past histories, will be compared and summarized between the groups. The outcome variables of all patients will also be summarized by treatment group and time, following descriptive statistics such as the number of patients, mean and standard deviation (or median and interquartile range) for continues variables, and relative frequencies for categorical variables. The number of participants included in each analysis will be reported, and we will adhere to the intention to treat principle regarding the group assignment.

Differences between the various treatments will be calculated using one-way ANOVA statistics; the follow-up data of each group will be statistically analyzed using ANOVA of repeated measures if they conformed to normal distribution and chi-square, and if they do not, the rank sum test will be used; logistic regression will be used to analyze the correlation between each treatment method and the efficacy. The study will categorize complications by types, such as infection, post-operative pain, nerve, blood vessel, tendon, or bone injury, and count them overall. Poisson regression analysis will be used with corrections for overdispersion when appropriate. The impact of treatment on complication rates will be expressed as MUA to intra-articular injection rate ratios. The safety of the treatment will be evaluated by identifying and summarizing any adverse events that occur during the study. All treatment effects will be reported with their 95% confidence intervals and *p*-values. The statistical analysis will be conducted using the IBM SPSS statistical package (version 25.0).

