### Informed consent process {26a}

All participants meet the inclusion criteria and agrees to participate will receive an information sheet and consent form. Before signing the informed consent, participants can discuss the study details with the clinicians and ask questions and take as much time as they need to consider their decision. The researchers conducting the study will obtain informed consent from the participants. All enrollment in the study will be subject to obtaining a signed consent form beforehand. After enrollment, full-time research assistants will conduct physical and imaging examinations and assign the treatment based on randomization. The results files of the participants will be coded, and personal data will not be disclosed.

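### The Allocation section contradicts itself and two other sections on whether randomisation and disclosure of the arm come before consent; if it is followed, acceptance can depend on the arm

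*Protocol article*

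**What the plan says.** The Allocation section sets out a sequence. Eligibility is confirmed on a CRF, and then: "The recruiting clinician will then contact the statistical staff for randomization". The next sentence reads: "The hospital staff will be informed of the allocation, but not the patient". The one after it reads: "The patient will be fully informed about the allocated therapy and given an information sheet to review before deciding to consent", with up to a week allowed for the decision. For those who decline, "If the patient does not consent, their reason for not doing so will be briefly recorded in a CRF". For the rest, "Those who consent will complete baseline forms and receive further treatments".

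Two other sections describe the opposite order. Recruitment states: "If the participant is eligible and agrees to participate, the clinicians will obtain informed consent and enroll the participant". After that enrolment, research assistants examine the patient and assign treatment from the randomisation. Informed consent process repeats that last step and states: "All enrollment in the study will be subject to obtaining a signed consent form beforehand".

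Table 1 (Participant timeline) places eligibility screen, consent and allocation in the same visit, days −7 to 0. On the analysis set, the statistical section on outcomes says that "we will adhere to the intention to treat principle regarding the group assignment".

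**The concern.** Randomisation protects the comparison only if what happens after it does not select patients differently in the two arms. A patient who already knows the arm when deciding on consent can accept or decline because of it. The two options differ in ways that could matter to patients. One is a procedure in an operating room, after fasting, under a brachial plexus block; the other is an injection session. The Background itself notes that patients with cuff injury who are considering manipulation may fear a further tear, and this trial enrols patients with cuff injury.

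If the refusers in one arm differ in prognosis from those in the other, both primary comparisons (total effective rate and change in Constant–Murley Score) are exposed to selection after randomisation. Analysis cannot undo this, because the only thing planned for a refuser is a short note of the reason.

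**Working it through.** **Step 1. The order in each place.**

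| Place | Order stated |
|---|---|
| Allocation | eligibility → randomisation → staff told → patient told → consent decision → baseline forms and treatment |
| Recruitment | eligibility → consent → enrolment → examinations and assignment from the randomisation |
| Informed consent process | signed consent → enrolment → examinations and assignment from the randomisation |
| Table 1 | consent and allocation at the same visit; order not settled |

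Allocation is also inconsistent internally: one sentence withholds the allocation from the patient and the next discloses it. They could describe successive moments (staff first, patient later). On either reading, randomisation still precedes consent and staff know the arm while consent is pending.

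**Step 2. Can intention to treat repair it?** Only if outcomes exist for all randomised patients. Under Allocation, baseline forms and treatment follow consent, and no follow-up is described for refusers. Analysing consenters by assigned arm does not restore the randomised groups.

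**Step 3. Illustrative size, continuous outcome.** There is no plan figure to reproduce. From the document: 160 per arm (Sample size) and a two-sided 5% test. Assumed: no true effect, SD 1, 5% of the injection arm refusing at random (152 remain), and a fraction *r* of the manipulation arm refusing whose mean outcome would have been *d* SD below average.

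- Bias = r·d / (1 − r)
- SE = √(1/n₁ + 1/152), with n₁ = 160(1 − r)
- False-positive rate = Φ(−1.96 + bias/SE) + Φ(−1.96 − bias/SE)

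| r | d | n₁ | Bias (SD) | SE | Bias/SE | False-positive rate |
|---|---|---|---|---|---|---|
| any | 0 | – | 0 | – | 0 | 5.0% |
| 10% | 0.3 | 144 | 0.033 | 0.116 | 0.29 | 5.9% |
| 15% | 0.5 | 136 | 0.088 | 0.118 | 0.75 | 11.6% |
| 20% | 0.5 | 128 | 0.125 | 0.120 | 1.04 | 18.1% |

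If refusers would have done better by the same *d*, the bias changes sign (against manipulation) and the two-sided rates are unchanged. If the 5% refusing injection are selected by the same *d*, subtract 0.05·d/0.95 from the bias; the rates become 5.3%, 8.2% and 13.0%.

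**Step 4. Illustrative size, binary outcome.** Assumed: no true effect, 160 allocated per arm, half with good and half with poor prognosis, success rates 30 points apart, and refusal only in the manipulation arm. The results use overall success rates of 0.428 and 0.645.

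| Refusal: poor / good prognosis | Share of arm refusing | Bias (points) | False-positive rate |
|---|---|---|---|
| 10% / 0% | 5% | 0.8 | 5.2% |
| 20% / 0% | 10% | 1.7 | 6.0–6.1% |
| 30% / 0% | 15% | 2.7 | 7.4–7.7% |
| 40% / 10% | 25% | 3.0 | 7.9–8.2% |

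For example, in the third row at 0.428: (0.5 × 0.578 + 0.35 × 0.278)/0.85 = 0.4545, which is 0.0265 above 0.428.

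**The case against.** The strongest reply is that Recruitment and Informed consent process both describe the conventional order, so the Allocation text may be a drafting fault and not what sites do. Table 1 also lists consent above allocation. This limits what can be claimed: the document does not show that patients were in fact randomised before consent. It does not remove the conflict, because Allocation is the section that governs allocation, it is explicit step by step, and row order within a single visit is weak evidence.

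A second reply is that differential refusal is conjecture. The protocol gives no refusal rates and describes both treatments as routine in the three hospitals. That stands. A reader might infer that refusals will depend on the arm and that the compared groups are therefore no longer the randomised ones. The documents support only that this can happen if the Allocation order is followed. Nor do they support a presumption that the bias would favour manipulation.

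A reader might also infer that refusals would use up the 10% dropout allowance and cost power. Nothing says that people who decline consent count as dropouts or within the 320. At the stated rates of 0.862 and 0.428, about 18 per arm would be enough for 80% power before dropout, so losing some of 160 has no practical consequence for power. The issue is selection, not numbers.

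**Conclusion.** The point holds as an internal contradiction with a conditional consequence. Allocation, as written, is incompatible with Recruitment and Informed consent process, and its two adjacent sentences disagree on whether the patient is told the arm. If it is followed, a route for selection after randomisation opens, and the intention-to-treat statement cannot be honoured for all randomised patients.

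Confidence is high on the textual conflict. The bias itself cannot be sized from the documents: it depends on refusal rates and on the prognosis of refusers, neither of which is given. It is zero when refusal is unrelated to prognosis. The figures of about 6–18% (continuous) and 5–8% (binary) rest wholly on the assumed scenarios and are not estimates for this trial. The correction is still necessary, because the loss could not be repaired at analysis and the remedy is nearly free.

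**What to change.** Rewrite Allocation to match Recruitment and Informed consent process: eligibility confirmed, signed consent covering both arms, baseline assessment, then randomisation. Delete the sentence that allows consent after the arm is known, and state once when, if at all, the patient is told the allocation.

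Recruitment began on 1 January 2023, so establish which order each site has used. Report the number of patients randomised before consent and the number refusing after allocation, by arm and site, with reasons. If there are any, add a sensitivity analysis restricted to patients who consented before allocation.

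The cost is a wording change to the protocol and the site procedures, with no extra patients or visits. The one visible downside is that the flow diagram may have to show refusals after randomisation.

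### The Allocation section places randomisation and disclosure of the arm before consent, contrary to the Recruitment and Informed consent sections, and Table 1 places allocation before the baseline scores; one order must be fixed

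*Protocol article*

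**What the plan says.** The protocol article describes entry into the trial in three text sections and one table.

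- **Allocation {16a} {16b} {16c}.** Once eligibility is confirmed on a CRF, "The recruiting clinician will then contact the statistical staff for randomization". Next, "The hospital staff will be informed of the allocation, but not the patient". The following sentence reads "The patient will be fully informed about the allocated therapy", and the patient is "given an information sheet to review before deciding to consent, which can take up to a week". A refusal is noted with its reason. Then: "Those who consent will complete baseline forms and receive further treatments". On the list itself, "The randomization will be stratified by participating site and done in blocks of four"; it is held by university statisticians alone, and a registered subject's record cannot be deleted.
- **Recruitment {15}.** Clinicians assess eligibility, obtain informed consent and enrol the patient. Research assistants then examine the patient and assign treatment by randomisation.
- **Informed consent process {26a}.** "All enrollment in the study will be subject to obtaining a signed consent form beforehand". Assignment again follows enrolment.
- **Table 1.** Eligibility, consent, allocation and a baseline questionnaire fall in visit 1 (day -7 to 0). The first ROM, CMS, MPQ, VAS and PPI fall in visit 2, the treatment day.

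The Outcomes paragraph {20a} of the statistical methods commits to intention to treat for group assignment. The abstract names the change in CMS as a primary outcome alongside the total effective rate.

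**The concern.** The order of consent, baseline measurement and randomisation decides whether the analysed groups are the randomised groups. Under the Allocation text, a patient accepts or declines the trial knowing the arm. The two arms differ visibly: one involves an operating room, fasting and a nerve block, the other injections. The section on ancillary and post-trial care says both are routine at these hospitals, so a patient who dislikes the assigned arm may be able to obtain the other outside the trial. Refusal that depends on the arm is therefore plausible. A refuser has been randomised but has no baseline form and no planned outcome.

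A baseline score given after the patient knows the arm can itself be influenced by that knowledge, and it then enters every change from baseline.

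**Working it through.** **1. The two orders side by side**

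| Step | Allocation {16a-c} | Recruitment {15} and Informed consent {26a} |
|---|---|---|
| 1 | Eligibility confirmed | Eligibility assessed |
| 2 | Recruiting clinician calls for randomisation | Consent signed |
| 3 | Hospital staff told the arm | Patient enrolled |
| 4 | Patient told the arm, then up to a week to decide | Examination and imaging by research assistants |
| 5 | Consent, or refusal with reason noted | Research assistants assign by randomisation |
| 6 | Consenters complete baseline forms; treatment | Treatment |

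The columns differ on when consent is given and on who triggers assignment. Within the left column, adjacent sentences disagree on whether the patient learns the allocation. Table 1 has consent and allocation in the same visit, so it does not settle the order.

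**2. Effect of refusal after allocation**

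Let r be the fraction of one arm that refuses, and let p_s and p_r be the effective rates in those who stay and those who refuse. The rate in the full randomised arm is (1 - r)p_s + r p_r. The rate observed in those who stay is therefore off by r(p_s - p_r), which is at most r in size.

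- The documents give neither r nor p_s - p_r. With r assumed at 0.05 to 0.15 in one arm only, refusals are 0.05 x 160 = 8 to 0.15 x 160 = 24. The bias in that arm's rate is then at most 5 to 15 percentage points.
- The planned difference is 0.862 - 0.428 = 0.434. A bias at the bound would not erase a difference that large, but it could create or hide a smaller one.
- Equal refusal counts would not remove the problem, because different kinds of patient may refuse each arm.

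**3. Baseline items exposed in Table 1**

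MPQ, VAS and PPI are patient-rated. In the CMS, pain (15 points) and the first three daily-living questions (part of 20 points) are self-assessed. Movement and strength, 40 + 25 = 65 of 100 points, are examiner items. The patient-rated share of the CMS is thus more than 15 and at most 35 points.

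**4. Blocks of four at 1:1**

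There are six equally likely blocks: AABB, ABAB, ABBA, BAAB, BABA and BBAA.

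- Positions fully determined by earlier ones: 2 each in AABB and BBAA, 1 each in the other four. That is 8 of 24, or 1/3, about 320/3 = 107 patients.
- Chance of a correct guess when always guessing the arm with fewer assignments so far and tossing a coin at ties: position 1, 1/2; position 2, 2/3; position 3, (2/3)(1/2) + 1/3 = 2/3; position 4, 1. The sum is 2.833, and 2.833/4 = 70.8%, against 50% by chance.

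Both figures require the guesser to know the block size and every earlier allocation at the site.

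**The case against.** **A drafting slip.** Two sections agree on consent first, and the Allocation section contradicts itself, so its consent text may simply be misplaced. This stands as far as it goes. A reader might infer that the trial does randomise before consent and that its arms are already selected, but the documents do not show which order sites use. The contradiction still has to be removed, and Table 1's baseline timing does not depend on it.

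**Block size.** A reader might infer that blocks of four make allocations predictable in general. The list is closed to everyone but the statisticians, the abstract names a central randomisation system, and two thirds of assignments stay uncertain even to someone tracking them. What remains is conditional: staff are told each allocation and clinicians are unblinded, so tracking within a site is possible. This part is secondary.

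**Screeners.** The Recruitment section says "The clinicians responsible for diagnosis and screening are unaware of the random grouping". A reader might see a contradiction with the clinician's call for randomisation. None is shown: the call follows confirmation of eligibility, so a screener can be unaware when judging eligibility and learn the arm later.

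**Baseline bias.** A reader might extend this to ROM and the whole CMS. ROM is measured by goniometer and most CMS points are examiner-rated. The Blinding section assigns assessments of clinical recovery to a blinded clinician. The exposure mainly concerns patient-rated items.

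**Numbers lost.** A reader might set 8 to 24 refusals against the 10% dropout allowance (16 per arm) and infer lost power. On the plan's stated rates, 55 to 59 per arm already give 99.9% power, and 160 - 24 = 136 remain. The harm is selection, which these counts do not measure.

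**Conclusion.** The contradiction is explicit and needs correction, because post-randomisation selection cannot be repaired in the analysis. Its consequence is conditional: if sites follow the Allocation section, arm-dependent refusal can bias the primary comparison, and the intention-to-treat commitment has no data with which to restore the refusers. The size of that bias cannot be derived from the documents. The bound of 5 to 15 points rests on an assumed refusal rate, confined to one arm, and on the most extreme difference between those who stay and those who refuse.

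Table 1 is a separate defect: it places allocation before the first outcome measurements, so MPQ, VAS, PPI and the self-assessed CMS items may be recorded with the arm known.

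**What to change.** 1. Use one order in every section: eligibility and MRI, signed consent, baseline ROM/CMS/MPQ/VAS/PPI, randomisation, disclosure, treatment. Remove the post-allocation consent text from the Allocation section, and state who requests the allocation and who learns it when.
2. In Table 1, move the baseline assessments ahead of Allocation.
3. Recruitment began on 1 January 2023, so changing the text alone could conceal a problem. Establish which order each site has used. Report every randomised patient by arm, including refusals after allocation with their reasons. The Allocation section already requires those reasons to be recorded and forbids deletion of records, so this is feasible.
4. For future patients, replace the single block size with randomly varying sizes (for example 4, 6 and 8) that are not disclosed to sites.

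The cost is an amendment to the wording, one visit re-ordered, a check of past practice at three sites, and a new list for the remaining patients. Varying block sizes give slightly looser balance within site.

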### Blinding (masking)

#### Blinding mechanism {17a}

Due to the nature of the intervention, comparing MUA and intra-articular injection treatment options, it is not possible to blind the clinicians to the allocation of treatment. However, they are strongly advised not to reveal the participant’s allocation status during follow-up assessments. An employee outside the research team will enter data into separate datasheets to ensure that the researchers who are responsible for the analyzation of the data do not have access to the information about allocation. The assessments of clinical recovery will be carried out by an experienced clinician who has undergone extensive training and is blind to treatment allocation.

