**Methods:**

A parallel, single-blinded, multi-center randomized controlled trial of 320 patients will be conducted at three hospitals of China. Eligible patients with frozen shoulder and rotator cuff injury or tear diagnosed by MRI will be randomly assigned to, in equal proportions, the manipulation under anesthesia group and the intra-articular steroid injection group via a central randomization system, undergoing a corresponding operation on day one and a sequent physical exercise for 14 days. The primary outcome is the comprehensive efficacy evaluation (total effective rate) and the change of Constant-Murley Score. Outcome assessors and data analysts will be blinded, and participants will be asked not to reveal their allocation to assessors.

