## Objectives {7}

The objective of this trial is to observe the safety and efficacy of MUA, compared to intra-articular steroid injection, in the treatment of FS patients diagnosed with rotator cuff injury or tear by MRI. We hypothesize that the course of the disease can be shortened by MUA with quicker functional recovery and gain in the range of motion and a subsequent faster return to work compared to steroid injection treatment. Also, preoperative and sequent MRI and musculoskeletal ultrasounds will be applied to patients before and 6 months post the intervention to evaluate the condition of the patient’s rotator cuff injury or tear.

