##### Safety evaluation

Adverse effects, including humeral shaft fracture, glenoid fracture, shoulder dislocation, complex regional pain syndrome, neurovascular lesions, and infection, will be recorded at any time during the trial. In addition, an MRI of the glenohumeral joint and a musculoskeletal ultrasound of the shoulder will be performed 6 months after treatment to assess the safety effects of the MUA on the rotator cuff.

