### Additional analyses {20b}

Based on the clinical observation indexes and shoulder joint MRI and musculoskeletal ultrasound imaging data before and after treatment of a total of 320 patients collected in the study, a multi-factor correlation analysis will be performed using subgroup analysis, sensitivity analysis, and logistic regression so that the following can be determined.1.1Whether there was a positive correlation between the shoulder joint active and passive mobility, pain and the data of the staging, and degree of rotator cuff injury characterized by shoulder MRI and musculoskeletal ultrasound imagining. During the MRI analysis, the primary analysis indicator used to assess the rotator cuff injury was the Ellman classification system [58], which takes into account both the tear's location and depth. There are two types of tears: partial-thickness tear (P) and full-thickness tear (F). For partial-thickness tears, they are categorized as follows: A: articular, B: bursal, C: intratendinous, and further graded as Grade 1 (<3 mm), Grade 2 (3−6 mm), and Grade 3 (>6 mm). For full-thickness tears, they are categorized based on the affected muscles: (A) supraspinatus, (B) infraspinatus, (C) teres minor, and (D) subscapularis and graded as Grade 1 (small, <2 cm), Grade 2 (large, 2–4 cm), Grade 3 (massive, >5 cm), and Grade 4 (cuff arthropathy). Since one of the most common complications of a rotator cuff tear is supraspinatus muscle atrophy [59], and fat infiltration is correlated with the severity of the rotator cuff tear [60], the secondary indicators will be Goutallier’s classification [61, 62] on fatty degeneration of cuff muscles and the Thomazeau classification of supraspinatus muscle atrophy [63]. Our designated medical professional will be responsible for interpreting all the MRI findings and comparing MRI images in later visits. This ensures integrity and accuracy in data analysis, minimizing the potential errors in data interpretation.1.2The type and the degree of rotator cuff injury for which the MUA is suitable, and the best indication for the maneuver.1.3Whether there is an increase in the degree of rotator cuff injury after MUA and to verify the safety of MUA on patients with rotator cuff injury.

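### The abstract promises blinded outcome assessors, but the operative text does not extend masking to the MRI and ultrasound reading that carries the cuff-safety conclusion

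*Protocol article*

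**What the plan says.** Four parts of the protocol article bear on who knows the treatment arm when the cuff is graded.

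- **Abstract, Methods.** The promise is general: "Outcome assessors and data analysts will be blinded, and participants will be asked not to reveal their allocation to assessors".
- **Blinding mechanism {17a}.** Treating clinicians cannot be blinded, and analysts are kept from the allocation. One blinded assessor is named, for one purpose: "The assessments of clinical recovery will be carried out by an experienced clinician who has undergone extensive training and is blind to treatment allocation".
- **Allocation {16a} {16b}{16c}.** Staff at the hospitals are told the assignment. No exception is made for anyone who reads images. Emergency unblinding {17b} likewise treats the researchers as knowing what each patient received.
- **Additional analyses {20b}.** On the MRI: "Our designated medical professional will be responsible for interpreting all the MRI findings and comparing MRI images in later visits". The justification follows at once: "This ensures integrity and accuracy in data analysis, minimizing the potential errors in data interpretation". Masking is not mentioned.

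The purpose of the imaging is stated under Objectives {7} ("preoperative and sequent MRI and musculoskeletal ultrasounds will be applied to patients before and 6 months post the intervention") and under Safety evaluation, which plans both kinds of scan for the same end: "musculoskeletal ultrasound of the shoulder will be performed 6 months after treatment to assess the safety effects of the MUA on the rotator cuff". Item 1.3 of Additional analyses {20b} then asks whether the cuff injury increased after MUA, and uses the answer to confirm that MUA is safe in these patients. No section names a reader for the ultrasound.

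**The concern.** Whether MUA damages an already injured cuff is the reason for studying this population. The Background says many physicians withhold MUA when the MRI shows cuff injury, for fear of causing a further tear. The imaging comparison is meant to answer that fear.

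The grading leaves room for judgement. Partial tears are classed by depth with cut-offs at 3 mm and 6 mm, so a borderline measurement can fall either side of a grade boundary. The team's expectation is also on record: the Background reports that, in its own experience, cuff injuries were not made worse by MUA. A reader who shares that expectation and knows the arm could under-call progression after MUA without intending to. The Discussion itself accepts that unblinded physicians may introduce bias, but the operative text puts nothing between that knowledge and the image grades.

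**Working it through.** The point is mainly textual, so the sections are set side by side first.

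| Question | Abstract | Blinding mechanism {17a} | Allocation | Additional analyses {20b} |
|---|---|---|---|---|
| Is the image reader masked to arm? | Only if counted among outcome assessors | Not addressed; blinded assessor is for clinical recovery | Hospital staff know the arm, no exemption | Not addressed |
| What safeguard is given for image reading? | General statement | None | None | One designated MRI reader |

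1. The default set by Allocation is that staff know the arm. Masking a particular reader therefore needs an exception.
2. The only named exception among assessors is the clinician who judges clinical recovery. Grading a tear on MRI or ultrasound is not naturally described that way.
3. The section that does deal with image reading relies on a single reader. That removes between-reader variation. It does nothing about a reader who knows the arm, because the same tendency would then run through every MUA image.
4. The abstract could be read to include the image reader. It does not say so, and the operative sections are narrower or point the other way.

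So an investigator could comply with every operative section and still have the cuff images graded with the arm known.

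**Illustration of size.** The documents give no progression rate and hence no figure of their own to reproduce. Inputs: 160 per group and 10% drop-out, from Sample size {14}; a progression rate of 5% to 10% in both arms, and 4 to 5 one-directional re-gradings, both assumed here.

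- Evaluable per arm: 160 × 0.90 = 144.
- Expected progressions per arm: 144 × 0.05 = 7.2; 144 × 0.10 = 14.4.
- Standard error of the difference, √(2p(1−p)/144): at 5%, √(0.095/144) = 2.6 percentage points; at 10%, √(0.18/144) = 3.5 points.
- Shift in the difference: 4/144 = 2.8 points; 5/144 = 3.5 points. Each is about one standard error at its rate.
- Share of MUA progressions removed: 4/7.2 = 56% at the 5% rate; 5/14.4 = 35% at the 10% rate.

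A handful of borderline calls would thus matter when progressions are few. The textual finding does not depend on these figures.

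**The case against.** The strongest reply is that masking is already promised. The abstract's statement has no limit to clinical outcomes, and whoever grades the cuff is, on a plain reading, an outcome assessor. The blinding section names a masked clinician for clinical recovery but does not say that other assessors are unmasked. Details of image de-identification could also sit in a full protocol or imaging manual that is not shown. This stands in part: the documents do not say that the image reader is unblinded, and nobody should report that they do. It does not dispose of the point. The article specifies the grading systems, the reader and the reason for trusting the reader, and the reason it gives does not address knowledge of the arm. The abstract's promise is also in tension with the section that informs hospital staff.

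Some stronger readings are tempting and are not supported.

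- A reader might infer that images are graded in known time order. For MRI this is a fair inference from the wording about comparing later visits, but it is not stated; for ultrasound there is no text at all. Scan order also applies to both arms alike, so by itself it does not favour MUA, and over-calling change on the later image would count against MUA.
- A reader might infer from Recruitment {15} that those who assign treatment also judge the cuff outcome, since "full-time research assistants will conduct physical and imaging examinations and assign the treatment based on randomization". That sentence concerns examinations after enrollment, with assignment named after them. It does not say that these assistants grade images or perform the 24-week ultrasound.
- A reader might infer that the whole safety conclusion rests on imaging. It does not: fractures, dislocation, neurovascular lesions, infection and other adverse events are recorded separately.

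**Conclusion.** The concern holds as a gap and an inconsistency in the blinding text. The abstract promises masking of outcome assessors, the operative rule confines the masked assessor to clinical recovery, hospital staff are told the arm, and the imaging section relies on one reader for accuracy. The MRI and ultrasound comparison that answers the cuff-safety question is therefore not protected from knowledge of treatment.

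It should be corrected, but its reach is limited. It touches the cuff component of safety and the imaging analyses in {20b}; it leaves the primary outcomes and the recording of clinical adverse events as they are. The size of any bias is unknown. The shift of about one standard error is illustrative and rests on the assumed 5–10% progression, equal rates in the two arms, 144 evaluable patients per arm, and re-gradings that all go one way. Even under those assumptions, the fall in the MUA progression rate ranges from roughly half at 5% to about a third at 10%.

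**What to change.** Reconcile the abstract, Allocation, Blinding mechanism {17a} and Additional analyses {20b} by extending the blinding rule to imaging:

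- The same designated reader grades all baseline and 24-week MRI, and the stored ultrasound images, with allocation and clinical notes removed.
- Patients from both arms are mixed in the reading list, and the grades are locked before unblinding.
- Allocation {16a} {16b}{16c} states that this reader is exempt from the notice of allocation given to hospital staff.

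Masking the scan date is optional. It would remove expectations tied to the later scan, but may reduce sensitivity to subtle change, which matters when missed progression is the worry. Whichever is chosen should be written down.

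The cost is a few sentences of protocol text, export of de-identified images and the reader's time for the ultrasound set; no additional scan or reader is required. The article does not say that ultrasound images are archived, so that should be confirmed. Scans already made can still be graded under these conditions if the images have been kept.
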